### Randomization Procedure

Participants will be randomized 1:1 to self-initiated care with our app (intervention) or standard care (control). Randomization and allocation will be performed by the author BS, using a web-based randomization tool (Castor EDC, Ciwit BV, Amsterdam, the Netherlands) to obtain variable blocks of two, four, or six, with stratification for treatment (conventional or biological DMARD). Castor builds the allocation sequence and performs randomization for the researcher, which can be considered centralized randomization, without the risk of allocation bias [24].

### Blinding

The 28-joint tender and swollen joint count for the primary outcome measure will be determined by a blinded research nurse or rheumatology resident. These individuals have no treatment relationship with the participants and will be instructed not to look at the patient files prior to the examination. The nurse or resident will be called during the study visit to perform the examination. As in most eHealth trials, it will not be possible to blind patients and health care providers caring for their patients to treatment allocation.

### Outcome Measures

The primary outcome measures are health care utilization, as measured by the number of outpatient clinic visits with a rheumatologist during the 12-month trial period, and disease activity, as measured by the DAS28-ESR at 12 months. A list of secondary outcome measures and their assessment time points are presented in Table 2 and Figure 5, respectively. The key secondary outcomes include cost evaluation of the intervention and adherence. Health care costs in the intervention group will be compared with usual care costs from a societal perspective as measured using the Treatment Inventory of Costs in Psychiatric Patients questionnaire, which is adjusted for use in RA patients, and medical information retrieved from the Reade EMR system [25]. Furthermore, explorative analysis will be performed to evaluate the relationship between user adherence and disease activity.

**Table 2 table2:** Secondary measures.

Secondary measure	Scale
Patient satisfaction	10-point Likert scale
Patient empowerment	Effective Consumer Scale 17
Disease activity	Routine Assessment of Patient Index Data 3
Treatment satisfaction	Treatment Satisfaction Questionnaire for Medication 9
Medication adherence	Compliance Questionnaire for Rheumatology 5
Work productivity	Work Productivity and Activity Impairment
Overall cost	Treatment Inventory of Costs^a^
Adherence	Questionnaire completion rates
Qualitative data	N/A^b^

^a^Adjusted for use in rheumatology.

^b^Not applicable.

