**Methods:**

This is a randomized controlled trial that will be performed for 1 year. A total of 176 patients with RA will be randomized to either self-initiated care with only one scheduled follow-up consultation assisted by our app or usual care. The coprimary outcome measures are the number of outpatient clinic consultations with a rheumatologist taking place during the trial period and the mean disease activity score as measured by the disease activity score 28 (DAS28) at 12 months. The secondary outcomes are patient satisfaction, adherence, patient empowerment, and cost evaluation of health care assisted by the app.

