### Objective

The objective of this paper is to report a protocol for a randomized controlled trial (RCT) that will test if we can safely (noninferiority in terms of Disease Activity Score [DAS] 28) reduce the number of outpatient clinic visits in patients with RA who self-monitor their disease. If the results confirm our hypothesis, we aim to implement our telemonitoring strategy in the Dutch health care system.

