### Flare

All patients, irrespective of the algorithm results or randomization arm, will be allowed acute outpatient visits if needed. If patients seek health care during the study, they will be seen by a rheumatology nurse. Patients will be asked about possible flares, associated symptoms, and medication adherence. If the rheumatology nurse cannot manage the flares, the patient’s own rheumatologist or the on-call rheumatologist (when the patient’s own rheumatologist is absent) will be notified by the rheumatology nurse for further treatment.

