### Power Analysis

To evaluate the safety of app-supported self-initiated care, we aim for noninferiority in terms of disease activity, as measured by the difference in the mean DAS28 score between the two study groups. Furthermore, we aim for superiority in terms of the number of outpatient clinic visits, with a lower number indicating a better result. Two sample size calculations are performed to determine an appropriate sample size for both hypotheses.

A sample size of 70 patients in each group has 90% power to detect noninferiority using a one-sided two-sample *t*-test. The margin of noninferiority is −0.3, and it corresponds to half of the minimal clinically important difference of 0.6, according to the EULAR response criteria. The true difference between means is assumed to be 0.0. The significance level (alpha) of the test is .05. The data are drawn from populations with a standard deviation of 0.60, which can be generally assumed in a stable group of patients with RA.

As the number of visits will be analyzed and each patient might have multiple visits, the sample size calculation needs to take the exposure-adjusted rate into consideration to power the study. Therefore, a Poisson test has been performed. The expected decrease in visits is approximately 50%, as a recent telemonitoring study in RA showed a decrease in visits of 58% [23]. A sample size of 22 patients in each group has 90% power at the 5% significance level to detect a difference of 25% (half the expected difference) with the use of a one-sided two-sample Poisson test. The exposure time is set at 6 months in the calculation, but with an actual follow-up of 1 year, the power will be even higher.

A sample size of 70 patients in each group will have sufficient power for both the clinical outcome and reduced appointment frequency. Considering these calculations and accounting for follow-up loss of 20% of patients, we plan to include 88 patients in each group (total 176 patients).

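### The health care utilization coprimary counts only rheumatologist visits, but the stated aim and conclusion cover all outpatient visits and health care use, and self-initiated care goes to a nurse first

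*Protocol article*

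**What the plan says.** Two places in the protocol article define the outcome, and both limit it to one type of provider. Outcome Measures has "health care utilization, as measured by the number of outpatient clinic visits with a rheumatologist during the 12-month trial period". The Methods part of the Abstract has "the number of outpatient clinic consultations with a rheumatologist taking place during the trial period".

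Three places state the aim or the conclusion without that limit. The Objective is to "reduce the number of outpatient clinic visits in patients with RA who self-monitor their disease". The Power Analysis states the hypothesis as "we aim for superiority in terms of the number of outpatient clinic visits, with a lower number indicating a better result". The Conclusions part of the Abstract says the trial will inform on lowering the use of health care.

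The Flare section sets the route for unscheduled care: "If patients seek health care during the study, they will be seen by a rheumatology nurse". A rheumatologist comes in at the next step: "If the rheumatology nurse cannot manage the flares, the patient’s own rheumatologist or the on-call rheumatologist" is to be informed by the nurse. The rule is not specific to one arm: "All patients, irrespective of the algorithm results or randomization arm, will be allowed acute outpatient visits if needed". The Algorithm section also has the app's alert direct the user to a rheumatology nurse.

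Study Design gives control patients visits planned by their rheumatologist, on average 2-3 a year. Intervention patients have one planned visit, at 12 months, with further visits for flares recognized by the app or at the patient's request.

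**The concern.** The strategy under test may change who delivers care as well as how much care is delivered. A planned control visit with the rheumatologist scores one. If a self-initiated contact in the intervention arm takes its place and the nurse resolves it, that contact scores zero. A lower count can therefore mean less outpatient care, or the same amount of care moved to nurses, and the coprimary cannot tell these apart.

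This matters because the conclusion is worded for the broader quantity. The Objective and the Conclusion section tie a positive result to implementing the strategy in Dutch health care. A reader would take success on an outcome labelled health care utilization as evidence that total outpatient use fell.

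**Working it through.** **Inputs from the article.** Control: 2-3 planned visits a year. Intervention: 1 planned visit a year, counted here as a rheumatologist visit. Nurse first for self-initiated contacts, in both arms. Evaluable patients: 70 per group. Test: one-sided 5% Poisson, 1 year of follow-up.

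**Not in the article.** Any rate of nurse contacts, any share of contacts that nurses resolve alone, and the control visit rate behind the visit-count sample size. The plan therefore has no figure of its own to reproduce on this point, and what follows is an illustration.

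**Assumptions.** Total contacts *C* per year are the same in both arms (2, 2.5 or 3), so the true all-contact ratio is 1.00. All control contacts are with a rheumatologist. The intervention arm has 1 planned visit and *C* − 1 self-initiated contacts. Nurses alone close a share *s* of these, and each of the rest becomes one rheumatologist visit.

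**Formulas.** Intervention rheumatologist rate: *I* = 1 + (*C* − 1)(1 − *s*). Rheumatologist-only rate ratio: *I*/*C*. Chance of declaring superiority: Φ{ ln(*C*/*I*) / √[(1/*C* + 1/*I*)/70] − 1.645 }.

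| *s* | *C* = 2 | *C* = 2.5 | *C* = 3 | Chance of declaring superiority |
|---|---|---|---|---|
| 25% | 1.75/2 = 0.88 | 2.125/2.5 = 0.85 | 2.5/3 = 0.83 | 29-55% |
| 50% | 1.5/2 = 0.75 | 1.75/2.5 = 0.70 | 2/3 = 0.67 | 72-98% |
| 75% | 1.25/2 = 0.63 | 1.375/2.5 = 0.55 | 1.5/3 = 0.50 | 96-100% |

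Example for *C* = 2.5, *s* = 50%: ln(2.5/1.75) = 0.357; √[(0.400 + 0.571)/70] = 0.118; 0.357/0.118 − 1.645 ≈ 1.38; Φ = 0.92.

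**Effect of control nurse contacts.** Keep *C* = 2.5 and *s* = 50%, but let 0.5 of the 2.5 control contacts be self-initiated and follow the same rule. The control rheumatologist rate is 2 + 0.5 × 0.5 = 2.25, and the ratio is 1.75/2.25 = 0.78 instead of 0.70. The gap shrinks but does not close, because 1.5 contacts a year are self-initiated in the intervention arm against 0.5 in the control arm.

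**The case against.** Several points count against the concern.

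- **The nurse-first rule covers both arms.** This stands. It would be wrong to say that control care is counted in full: acute control contacts closed by a nurse are also left out. The imbalance comes only from the larger self-initiated share in the intervention arm.
- **The size is unknown.** This stands. A reader might infer that a large reported saving could be no saving at all. With 2.5 control visits, 1 planned intervention visit and 1.5 nurse contacts in the intervention arm, the rheumatologist-only ratio is 1/2.5 = 0.40, while the all-contact ratio is (1 + 1.5)/2.5 = 1.00. That requires nurses to close every self-initiated contact and control patients to have no nurse contacts, and the article supports neither. With 0.5 control nurse contacts a year the all-contact ratio is 2.5/3.0 = 0.83.
- **Other intervention-arm contacts.** A reader might add the 6-month blood test as uncounted care. It is a laboratory test with results by telephone, not a consultation, and the article does not describe laboratory monitoring of controls, so no imbalance follows from it.
- **A lower count is expected from the design.** This is true of any strategy that removes planned visits, and it would hold for an all-contact count too. It is no fault of this outcome.
- **The cost evaluation may capture nurse care.** This stands in part. It uses a cost questionnaire and EMR data, but it is secondary and measures cost. Nurse and telephone contacts are not listed as an outcome in Outcome Measures or Table 2.
- **The two defining passages agree, and the rest is shorthand.** This is fair for visits against consultations. It is less convincing for the Power Analysis, which states the superiority hypothesis without a provider limit, and for the Abstract's Conclusions, which widen the claim to health care use.

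**Conclusion.** The concern holds as a mismatch between what is counted and what is to be concluded. A count of rheumatologist visits is a legitimate coprimary if it is named as such. The article does not support the stronger inference that the outcome is invalid and must be replaced, and replacing a coprimary with 78 patients already randomized would be debatable. What the count cannot support alone is a claim of fewer outpatient visits or lower health care use.

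In the illustration, a rheumatologist-only ratio anywhere from 0.50 to 0.88 is compatible with no fall in total contacts. That range rests on equal total contacts, no control nurse contacts, and nurses closing 25-75% of self-initiated contacts; the article gives none of these. Control nurse contacts would bring the ratio nearer to 1. The correction is a cheap improvement that changes what the trial can conclude.

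**What to change.** 1. Name the coprimary rheumatologist visits, and use that wording in the Abstract's Methods, the Objective, the Power Analysis and Outcome Measures.
2. Prespecify a companion count of all RA-related outpatient contacts over 12 months (rheumatologist, nurse and telephone). Take it from the EMR by one rule in both arms, exclude study-only visits in both arms, and report it by provider.
3. State in advance that reduced health care use, or fewer outpatient visits, will be claimed only if the all-contact count is also lower. Otherwise the conclusion is limited to rheumatologist visits. Word the Abstract's Conclusions to match.

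The cost is a change of wording and a slightly wider EMR query; the EMR is already a source for the cost evaluation. Patient care and the coprimary count itself stay as they are. The downside is that the reduction in all contacts will probably be smaller than the approximately 50% fall in visits that the Power Analysis expects.

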## Results

Recruitment is currently underway. We started recruitment in May 2019, and it will continue until the goal of 176 participants is reached. Thus far, 78 patients have been randomized and, empirically, experiences with the app have been positive. Data release in the form of a research paper is estimated by the end of 2021.

## Discussion

### Summary and Strengths

This study will be the first randomized trial to test the safety and efficacy of self-initiated care supported by a smartphone app in patients with RA. Although several apps to monitor disease activity exist and some of these apps have been tested, to date, no studies have reported on the use of an app to support patient-initiated care [26-28]. This study has been performed in accordance with the relevant domains of the model for assessment of telemedicine applications, as advised by the European Commission guidelines, and meets the requirements of the checklist on how to report health interventions using mobile phones [29,30].

In a recent systematic review of mobile apps for monitoring disease activity, a lack of high-quality apps was reported [11]. The review suggested that apps should use validated questionnaires and have a user-friendly interface. With the design and redesign strategy and patient feedback in all stages, we were able to develop a mobile app that meets the review requirements. The app is easy for patients to use, visually presents data, and incorporates useful information for physicians. Furthermore, we secured technical support during the trial period, as one of the developers of the app is a part of the project team (FC). Additionally, we have ensured that this system is integrated with the existing Reade EMR system to optimize clinicians’ workflow in their busy daily clinical practice. Integration of the app and its patient-reported outcome (PRO) data with the existing EMR system has enormous research potential. This has been recognized before but is often not accomplished [31].

### Expectations

We anticipate that the app will facilitate better comanagement of the disease by rheumatologists and patients. This will result in early identification of disease flares and will lead to possibly better interventions for patients requiring treatment adaptation. Moreover, we expect a reduced appointment frequency for patients, as unnecessary consultations will be prevented [23]. Furthermore, self-monitoring will improve patient engagement and empower patients to manage their own illness. We expect a fair amount of missing data from the app owing to varying engagements from our patients [32]. Our primary objective is not to use the PRO data in statistical analyses, but to ensure that the data are useful to patients and rheumatologists for monitoring and understanding the disease. Even if patients enter data only once every 4 weeks, they will still have 4-6 times more data about their disease status when compared with the data obtained on visiting the rheumatology outpatient clinic every 4-6 months.

### Limitations

This study has several potential limitations. First, there is a possibility of a ceiling effect of the secondary outcome measures, as all participants will have low disease activity at baseline and a disease duration of at least 2 years and might score well in several of the secondary outcome measures, as is often the case in the Dutch health care system. Second, the addition of a third arm (patient-initiated care without the app) has been discussed to allow evaluation of the effect of the app. However, we opted against the inclusion of a third arm because this would mean that information about disease activity could be lacking for a full year, which is against current EULAR guidelines. To avoid this unethical design, we selected a design similar to that used in the study by de Jong et al, in which the telemedicine system IBDcoach led to a reduction in outpatient clinic visits when compared with usual care [2]. Third, generalizability is limited for three reasons. Firstly, we only include patients who are in remission, and thus, patients with high disease activity are excluded from this intervention. Nevertheless, we think that this intervention is still very relevant, as there are unmet needs to reduce the number of outpatient clinic visits and detect flares early. Secondly, only patients who own a mobile device and therefore are likely receptive to mobile technology are included. However, we anticipate that this selection excludes only a small percentage of individuals, as the proportion of adults with a smartphone is growing and is already at 87% [16]. Thirdly, the MijnReuma Reade App is only accessible to patients at Reade presently, which limits delivery at scale. We have however granted everyone access to the prototype app, which other hospitals can incorporate into their own EMR systems.

### Conclusion

Following a design, test, and redesign approach, we have developed an app that allows patients with RA to monitor their own disease activity. We anticipate that our app will safely lower the need of patients for outpatient clinic visits. If proven safe and effective in an RCT, our aim is to implement our telemonitoring strategy in the Dutch health care system.

## Appendix

Multimedia Appendix 1 The SPIRIT checklist.

## Abbreviations

DAS28: disease activity score 28
DMARD: disease-modifying antirheumatic drug
EMR: electronic medical record
ESR: erythrocyte sedimentation rate
EULAR: European League Against Rheumatism
FQ: flare questionnaire
IBD: inflammatory bowel disease
PRO: patient-reported outcome
RA: rheumatoid arthritis
RAPID3: Routine Assessment of Patient Index Data 3
RCT: randomized controlled trial
